#### Quality assurance of treatment delivery

All treatment sessions are video-recorded (the participant is not visible) for the purpose of supervision in order to prevent practitioner drift. These are independently evaluated to rate the delivery of the essential and unique components of each treatment using an instrument adapted from the UKATT process rating scale
[36].

### Recruitment

Recruitment was originally planned to continue for 8 months. However, due to an unexpected delay in the commencement of recruitment, combined with the additional factor of a hard end date for recruitment, this was reduced to 5 months.

#### Sample size calculation

Originally the trial had planned to use 6 therapists over 8 months. It was estimated from current case loads that 4 therapists can screen a maximum of 384 patients in 6 months. Of these, 113 (29.4%) would engage with the specialist service. The maximum number screened over 8 months was estimated at 768 or 96 per month. Using the number interested in being treated as an estimate of those who would consent to the trial, the maximum number we could have recruited was approximately 222 (that is, 111 in each group) which is 28 per month. Based on experience in previous studies where loss to follow-up has been in the region of 20%, we erred on the side of caution, allowing for a follow-up rate of 70%. This should have resulted in approximately 77 patients in each group. With 77 patients in each group, using 80% power, two-sided 5% significance, we would have been able to detect an effect size difference of 0.45 on the AUDIT score at month 6.

However, because the recruitment period has been reduced to 5 months, the maximum number that can be screened is 480, of which we could potentially recruit 140. Using the same follow-up rates, power and significance as before, this would enable an effect size difference of 0.57 on the AUDIT score at month 6 to be detected.

### Analysis

The main aims of this pilot study are to evaluate the acceptability of the interventions to the participants, and the elements and processes of the design. Using the opportunity available to compare the effectiveness of the two interventions and advising whether one or both could be taken forward into a large-scale study, the planned analyses cover all aspects.

#### Qualitative analysis

Interviews are digitally recorded (where consent is given), fully transcribed and imported into Atlas.ti
[37] for the management and analysis of data. Thematic analysis will be used to identify themes by their frequency, intensity and extensiveness, a technique described by Braun and Clarke
[38].

#### Primary statistical analysis

The primary patient outcome measure for the study is the AUDIT score measured at 6 months. Analysis will be on an intention-to-treat basis using two-sided, 5% significance and will compare outcomes for the alcohol-focused intervention with outcomes for the healthy living intervention at 6 months.

The AUDIT scores at 6 months will be analyzed using a linear regression model. The baseline AUDIT score will be included as a covariate and the model will also include the treatment group. Model checking will be performed to ensure that the model is a good fit for the data. If necessary, transformations will be used to improve model fit.

#### Secondary statistical analyses

Secondary outcomes include the AUDIT score at month 12. They also include LDQ, SSQ, CORE-10 and EQ-5D all measured at 6 and 12 months. These will be analyzed separately for each time point using linear regression models, adjusted for the baseline score of the dependent variable and include a variable for treatment group. All analyses will compare the alcohol-focused intervention with the healthy living intervention.

Abstinence, a binary outcome (yes/no) collected at month 6 and month 12, will be analyzed using logistic regression models for each time point. Included in the models will be a variable for treatment group and baseline AUDIT score.

Preference for treatment will be collected prior to randomization and will be summarized overall and by treatment group. The primary analysis will be repeated but with the addition of the variable for treatment preference and a variable for the interaction between preference and treatment group to examine the effect preference may have on outcomes.

The relationship between client and therapist as measured by the WAI will be explored using descriptive statistics and correlation where appropriate. We will undertake an exploratory analysis to investigate the effect of adherence to treatment using a complier average causal effect analysis
[39,40]. The numbers of adherent participants and further details of adherence will also be summarized.

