### Participants and setting

The study is being undertaken in two general hospitals where alcohol-related admissions have been increasing year on year
[21]. Preparatory studies in our program of research used a two-stage process to identify wards with a) the highest rates of admissions of patients with alcohol-related diagnoses and b) where there would be benefit from treating the alcohol problem. These wards are the main but not exclusive source of recruitment of patients into the study.

Staff from the local NHS addiction treatment unit currently provide an in-reach service to these hospitals, which aims to engage patients in specialist treatment and effect an early hospital discharge. The in-reach team are responsible for recruiting and providing treatment to the study participants. All patients admitted to the target wards are considered potential participants if they meet the eligibility criteria.

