#### Consent procedure

Potential participants are provided with a verbal explanation of the study and a copy of the PIS. The PIS outlines the purpose of the study, the proposed interventions, study processes and time commitment required for both treatment and follow-up assessments. For those agreeing to participate, written consent is obtained and a baseline questionnaire is completed. An additional PIS gives information and asks for consent to participate in the qualitative element of the study.

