#### Randomization process

Six therapists are divided into three pairs, broadly matched on experience and qualifications. Within each pair, one therapist is trained to deliver the alcohol-focused intervention and the other trained to deliver the healthy living treatment. Each participant is randomized such that they have a 50:50 chance of getting the therapist who screened them or the matched colleague. This approach is based on previously obtained opinions from service users stating that continuity of care is important to them. Should one of the therapists in the pair not be available due to illness or similar reasons, the participant is allocated to a therapist within a different pair at the point of randomization. Participants are randomized by a secure remote computer service run by the fully registered York Trials Unit, to either an alcohol-focused intervention (control treatment) or a healthy living intervention.

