#### Training

Six addiction practitioners working in the hospital in-reach team received dedicated training covering the study’s procedures and the practices and techniques of each intervention, followed by supervised practice of study treatments until deemed competent. The training package is delivered separately to the two treatment groups by an experienced trainer/addiction psychologist. Once deemed competent, practitioners continue to deliver the manually guided study interventions under regular supervision based on recorded practice to avoid therapist drift. Additional training is given on the study protocol process, documentation completion and obtaining informed consent.

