Recruitment rates are presented in three tiers: number screened, number eligible and number participating, with the last of these used to infer initial acceptability. Retention in treatment is evaluated by the number of sessions attended and used as a measure of treatment acceptability. Quantitative assessment of the acceptability of the postal follow-up questionnaires is assessed by return rates and completion rates. Qualitative assessment of any issues regarding questionnaire completion is explored during the interviews. Patients’ reported preferences for either or neither of the study interventions are collected in the baseline questionnaire, prior to randomization.

All follow-up data are collected by postal questionnaire at 6 and 12 months post randomization with postal reminders sent 2 and 4 weeks after initial correspondence. In the event of a participant failing to complete their questionnaires, attempts to obtain at least the primary outcome data are made via telephone.

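### The preference-by-treatment interaction would absorb any effect of keeping the recruiting therapist, to the extent that stated preference follows that therapist's arm; a table and a sensitivity model would show whether it does

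*Protocol article*

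**What the plan says.** All references are to the Protocol article.

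- **Participants and setting:** "The in-reach team are responsible for recruiting and providing treatment to the study participants".
- **Randomization process:** "Within each pair, one therapist is trained to deliver the alcohol-focused intervention and the other trained to deliver the healthy living treatment". Then: "Each participant is randomized such that they have a 50:50 chance of getting the therapist who screened them or the matched colleague". The stated reason is that service users value continuity of care. The exception is that, if one of the pair is unavailable, "the participant is allocated to a therapist within a different pair at the point of randomization".
- **Training:** "The training package is delivered separately to the two treatment groups by an experienced trainer/addiction psychologist".
- **Consent procedure:** "Potential participants are provided with a verbal explanation of the study and a copy of the PIS". Consent and the baseline questionnaire follow.
- **Patient outcome measures:** "reported preferences for either or neither of the study interventions are collected in the baseline questionnaire, prior to randomization".
- **Primary statistical analysis:** a linear regression of 6-month AUDIT on baseline AUDIT and treatment group.
- **Secondary statistical analyses:** preference is summarized overall and by treatment group. The primary model is then rerun with "the addition of the variable for treatment preference and a variable for the interaction between preference and treatment group", to study how preference may affect outcomes. No term for the recruiting therapist is named.

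**The concern.** By the time participants state a preference, they have met a therapist who delivers one of the two interventions. Some may lean towards that therapist's intervention, or towards that person. Apart from cross-pair cover, a participant keeps the recruiter exactly when the allocated arm is the recruiter's arm. For anyone whose preference matches the recruiter's arm, receiving the preferred treatment and keeping the therapist are then the same event. A model with only preference, treatment and their product cannot tell the two apart.

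The planned summary would not reveal this. Allocation is random with respect to the recruiter's arm, so preference by treatment group would look balanced even if every participant simply preferred what the recruiter delivers.

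Establishing preferences is a listed aim, acceptability is the pilot's main purpose, and the Discussion says the findings will feed into a multi-centre trial. A continuity effect read as a preference effect would send that design in the wrong direction.

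**Working it through.** **The plan's own figure.** Sample size calculation gives 140 recruited and 70% follow-up: 140 x 0.70 = 98 analysed, 49 per arm. The detectable effect at 80% power and two-sided 5% is (1.960 + 0.842) x sqrt(2/49) = 0.566 SD by the normal approximation and 0.572 by the t-test. The stated 0.57 is reproduced. The article gives no figure for the preference interaction.

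**Assumptions.** The document supplies neither of these quantities:
- q = the chance that stated preference equals the recruiter's arm;
- c = the benefit of keeping the therapist, in SD of AUDIT.

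The therapist who screens is also taken to be the one who recruits, recruiters are balanced between arms, and the two preference groups are equal in size.

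**Chance of keeping the therapist, by cell:**

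| | Allocated healthy living | Allocated alcohol-focused |
|---|---|---|
| Prefers healthy living | q | 1-q |
| Prefers alcohol-focused | 1-q | q |

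The interaction is the difference between preference groups in the treatment effect. Continuity contributes [q - (1-q)] - [(1-q) - q] = 2(2q-1), times c. The bias is therefore **2(2q-1)c**.

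**Standard error.** Four cells of 98/4 = 24.5 give sqrt(4/24.5) = 0.404 SD.

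**Results at c = 0.3 with no true preference effect** (rejection rates simulated at N = 98, 6,000 runs per setting):

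| q | Bias (SD) | Bias / SE | Rejection at nominal 5% |
|---|---|---|---|
| 0.5 | 0 | 0 | about 5% |
| 0.6 | 0.12 | 0.30 | about 6% |
| 0.7 | 0.24 | 0.59 | about 9% |
| 0.8 | 0.36 | 0.89 | about 13% |

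At q = 0.8 the bias is 0.24 SD for c = 0.2 and 0.60 SD for c = 0.5, with rejection about 9% and 29%.

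**Effect of adjustment.** Adding recruiter's arm and recruiter's arm x treatment brought the simulated bias to about zero and rejection to about 5% in every setting. The price is precision. The variance of the interaction is multiplied by roughly 1/[1 - (2q-1)^2], so the SE grows by 1.09, 1.25 and 1.67 at q = 0.7, 0.8 and 0.9. In simulation at N = 98 the factors were about 1.1, 1.3 and 1.8 to 1.9.

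**Bias against variance at q = 0.8.** With c = 0.2, adjustment removes a squared bias of 0.24^2 = 0.058 but adds variance of about 0.163 x (1/0.64 - 1) = 0.092, a net loss. With c = 0.5 it removes 0.60^2 = 0.36 for the same added variance, a clear gain.

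**The case against.** A reader might infer from the design that the interaction **is** confounded. The document does not support that. Nothing says that participants know which intervention their recruiter delivers, who administers the preference item, or that preference varies by recruiter. Every participant receives written information on both interventions before consenting. That service users value continuity does not show that it changes AUDIT. Recording preference before randomization is correct practice in itself. This objection stands, and it makes the point conditional.

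A reader might also infer that the treatment comparison is biased, or that the overall preference split is distorted by who recruited whom. Allocation is random with respect to the recruiter, so the primary analysis is not affected. For the split, there are three therapists per arm and no imbalance in screening is documented, so distortion is not established.

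The size is modest. Each bias tabulated above is below one SE, and significance needs about 1.96 x 0.404 = 0.79 SD, so at c = 0.3 and q up to 0.8 continuity alone would not be expected to produce a significant interaction. Participants preferring neither intervention and cross-pair cover weaken the link further. All of this stands, and it limits the importance of the point in a secondary analysis of a pilot.

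Finally, an article may leave sensitivity models to the analysis plan. That is true in general. Here, however, the article names the model's terms and its descriptive table, and neither can show whether preference follows the recruiter.

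**Conclusion.** The point holds in conditional form. The interaction would be confounded with keeping the recruiting therapist to the extent that stated preference tracks the recruiter's arm and continuity affects AUDIT. The design makes the first possible and gives some reason to consider the second, but the document demonstrates neither. Both would have to hold, since either one absent removes the bias entirely. The size rests on assumed q and c, and at the values shown it would mislead the reading of a point estimate more often than it would produce a false significant result. This is an inexpensive improvement to a secondary analysis, not a flaw in the trial's main comparison.

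**What to change.** 1. In addition to the planned summary by treatment group, tabulate preference (including neither) by the arm of the recruiting therapist. This table shows directly whether preference follows the recruiter.
2. Keep the planned preference model. Report beside it a sensitivity model that adds recruiter's arm and recruiter's arm x treatment; the latter is the continuity term. Do not replace the planned model, because at moderate c the variance added can exceed the bias removed.
3. State in advance that a positive interaction will be read as a preference effect only if it persists in the sensitivity model.
4. If preference follows the recruiter almost completely, report that the two effects cannot be separated at this sample size.

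The cost is one table and two model terms. No new data should be needed, because randomization within the screening therapist's pair already requires knowing who that therapist is. The interaction in the sensitivity model will be less precise, as shown in the working.

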#### Economic analysis

The economic component of the study comprises a cost-effectiveness and cost-utility analysis, and aims to identify, quantify and value health-care resources utilized by participants in each trial arm.

Resources utilized in the identification and delivery of the alcohol-focused and healthy living interventions will be recorded. This will allow the calculation of costs related to the implementation of these interventions. Local costs will be used to calculate the costs of the interventions. In addition, specific training costs for staff are calculated in terms of staff time, costs for premises and the cost of training materials.

Participants’ use of health care will be identified retrospectively using service use questions and applying a common set of national unit cost estimates
[41,42]. Participant costs in the 6-month period before the intervention can then be compared to costs in the 6-month period after receiving the intervention and used to explore any changes in costs imposed by participants in each group.

The economic analysis will calculate the incremental cost-effectiveness of the alcohol-focused intervention compared to the healthy living intervention, using measures of clinical outcome and quality of life (EQ-5D
[33]) responses at baseline and at 6 and 12 month follow-up. The use of EQ-5D enables the estimation of quality-adjusted life years (QALYs). Data will be bootstrapped to account for the expected skewness evident in economic cost data. The analysis will construct cost-effectiveness acceptability curves to illustrate the probability that the alcohol-focused intervention is more cost-effective than healthy living, based on different monetary values being attached to the QALYs. The use of QALYs follows the recommendations of the National Institute for Health and Clinical Excellence
[43] and enables the value for money afforded by treatment to be compared to a range of other health-care interventions.

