### Eligibility criteria

Patients are eligible if they:

– are admitted to one of the hospitals with a diagnosis thought likely to be responsive to addiction interventions

– score equal to or more than 16 on the Alcohol Use Disorders Identification Test (AUDIT)

– are aged 18 years and over (males and females)

– are willing and able to give written informed consent

Patients are excluded if they:

– have received specialist treatment with a primary focus on alcohol in the past 6 weeks

– have no fixed abode (that is, are not available for follow-up)

– are currently serving a sentence in prison or have outstanding legal issues likely to lead to imprisonment

– have a mental or physical illness likely to preclude active participation in treatment or follow-up (for example, are not stable through current medication or treatment)

– are unwilling or unable to give written informed consent

– are unable to take part in either intervention using spoken English or are unable to self-complete the validated English language outcome measure tools

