#### Intervention content

Both interventions are delivered in four sessions using motivational dialogue based on the guiding principles of motivational interviewing
[23]. This number of sessions has been determined using evidence from the UK Alcohol Treatment Trial (UKATT), which suggest optimal attendance is achieved over four sessions
[24].

Each intervention consists of four sessions of 30 to 45 minutes each, delivered one to two weeks apart, over a maximum period of 8 weeks. Sessions for either arm can be delivered at the specialist clinic, the participant’s home or at a mutually agreed suitable alternative location as is current practice for the Hospital In-Reach Team (HIRT).

Both interventions involve prompting the formation of intention through encouraging participants to set a general goal or make a behavioral resolution, and encouraging them to set specific goals, self-monitor behavior using a diary. Feedback from the participant on their performance allows them to review the behavioral goals together with the therapist. Motivational dialogue is used to elicit behavior change by helping clients explore and resolve ambivalence and facilitate treatment goal-setting
[20].

The alcohol-focused intervention (iSBNT) is a social-network-based, cognitive behavioral intervention using motivational dialogue
[20] and drawing on cognitive behavioral therapy (CBT), which has been shown to be an effective approach for treating patients with alcohol problems
[25-27]. It has a strong evidence base in UK clinical trials and is increasingly commonly taught and practiced in the UK addiction field. It contains exclusively drinking behavior change topics and involves strengthening coping skills and confidence, with emphasis on structure and skill rehearsal. Behavioral rehearsal is used incrementally to develop the service user’s and network members’ skill levels and confidence to apply new skills in their own environment. Homework is used to implement new practice and facilitate achievement of agreed treatment goals.

The participant is encouraged to recruit a supportive network of concerned others, who will help the participant to implement behavior change and develop new lifestyle habits inconsistent with drinking. The network is encouraged to make plans to cope with relapse risks and actual relapse, providing support for each other where necessary.

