#### Patient outcome measures

This study also provides an opportunity to compare the effectiveness of the two interventions. Therefore, the AUDIT score at 6 months post randomization has been designated as the main patient outcome and is also measured at 12 months post randomization, whilst the proportion of participants who have not consumed any alcohol in the previous 6 months is collected via a yes/no question at 6 and 12 months post randomization.

A number of secondary patient outcomes are also measured. The Leeds Dependence Questionnaire (LDQ)
[29], a ten-item, self-administered measure designed to assess severity of dependence is helpful in determining a patient’s treatment goals
[30]. Social satisfaction is measured using the Social Satisfaction Questionnaire (SSQ), a validated eight-item scale found to be a suitable outcome measure in people with substance use disorders covering social domains that are likely to be important to, and engage, service users in treatment
[31].

Subjective well-being, psychological problems and functioning are measured using the Clinical Outcomes in Routine Evaluation (CORE-10)
[32]. The health-related quality of life (HRQoL) is assessed using the European Quality of Life – 5 Dimensions (EQ-5D). The EQ-5D is a standardized measure of health status developed by the EuroQol Group in order to provide a simple, generic measure of health for clinical and economic appraisal, where health is characterized on five dimensions (mobility, self-care, ability to undertake usual activities, pain and anxiety/depression)
[33]. These four measures are taken at baseline, and 6 and 12 months post randomization.

At the end of the second and third treatment sessions, both participant and therapist are asked to complete the 12-item (short version) working alliance inventory (WAI)
[34] in order to assess the participant–therapist relationship.

The costs of delivering the two interventions are calculated on the basis of resources used. Participant use of health services, other alcohol services outside the study, public services and criminal justice services is assessed through service use-questions at baseline, and 6 and 12 months post randomization. We will use utility values based on societal values using the York tariff
[35].

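### The before-after cost comparison in the economic analysis will show a fall in both arms whether or not treatment works, and its after window does not match the service-use questionnaires

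*Protocol article*

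**What the plan says.** The Economic analysis section of the protocol article describes two uses of the cost data.

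- A before-after comparison: "Participant costs in the 6-month period before the intervention can then be compared to costs in the 6-month period after receiving the intervention". Its stated purpose is exploratory, the result being "used to explore any changes in costs imposed by participants in each group".
- The main comparison, between the randomized arms: "The economic analysis will calculate the incremental cost-effectiveness of the alcohol-focused intervention compared to the healthy living intervention". It draws on EQ-5D "responses at baseline and at 6 and 12 month follow-up", and on skewed costs it adds: "Data will be bootstrapped to account for the expected skewness evident in economic cost data".

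Three other sections bear on the first of these.

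- Eligibility criteria: patients qualify if they "are admitted to one of the hospitals with a diagnosis thought likely to be responsive to addiction interventions".
- Patient outcome measures: use of services "is assessed through service use-questions at baseline, and 6 and 12 months post randomization".
- Intervention content: the four sessions are "delivered one to two weeks apart, over a maximum period of 8 weeks".

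**The concern.** Two features make the before-after comparison uninformative about treatment.

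First, participants are selected at a peak of health-service use. A person found on a ward has, on average, used more care recently than is usual for that person, and later use drifts back towards the usual level. If the index admission itself is counted in the before window, the fall is larger. The text does not say whether it is counted. Both arms receive an active intervention, so no group shows what would have happened without one.

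Second, the after window is defined from receipt of the intervention, while the questionnaires are timed from randomization. No single questionnaire measures the window that the sentence describes.

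At stake is how a cost result is read. The Background says that specialist treatment can reduce health-care use and costs, commissioners are among the collaborators, and the findings are to shape a multi-center trial. A fall in cost within each arm could easily be taken as a saving due to the interventions.

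**Working it through.** **Number analysed per arm.** The Sample size calculation section gives 140 recruits and 70% follow-up: 140 / 2 = 70 per arm and 70 x 0.70 = 49. The section's own figure reproduces with this number: (1.960 + 0.842) x sqrt(2/49) = 0.566 by the normal approximation, and 0.572 by the noncentral t, against the stated 0.57. The economic section states no figure to reproduce, so the rest is an illustration under assumptions.

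**Why the fall appears.** Let B be a participant's usual six-month cost, with the same expectation before and after, and A the cost of the index admission if it is counted in the before window. With no treatment effect:

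- within-arm change: E(after) - E(before) = B - (B + A) = -A, in each arm;
- between-arm difference in change: (-A) - (-A) = 0.

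Regression to the mean makes the first line more negative. It has the same expectation in both randomized arms, so the second line does not move.

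**Simulation, no treatment effect, 49 per arm, 4000 repeats.** Assumed: each person's mean cost is drawn from an exponential distribution with mean 1000 units per six months, with exponential variation around it in each window. A is 1000, 2000 or 4000 units. All cost values are assumptions, because the article gives none.

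| A | Within-arm change | Between-arm difference in change, mean (SD) | Between-arm difference in follow-up cost, mean (SD) |
|---|---|---|---|
| 1000 | -998 | +3 (397) | -3 (350) |
| 2000 | -1991 | +6 (405) | +2 (355) |
| 4000 | -4005 | -7 (411) | +6 (352) |

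The Monte Carlo error of the between-arm means is about 400 / sqrt(4000) = 6, so they are compatible with zero. The within-arm fall equals A by construction. The simulation leaves out regression to the mean, which would add to the fall.

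**Which between-arm estimate is better.** In this model the variance of a six-month cost is 3,000,000 (SD 1732) and the before-after covariance is 1,000,000, so the correlation is 1/3. The standard error of the arm difference is:

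- change scores: sqrt(2 x (3,000,000 - 1,000,000)) x sqrt(2/49) = 2000 x 0.202 = 404;
- follow-up cost alone: 1732 x 0.202 = 350;
- follow-up cost with baseline cost as covariate, large-sample: 350 x sqrt(1 - 1/9) = 330.

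At this correlation the change score is the least precise of the three and the covariate-adjusted difference the most precise.

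**The after window.** Take 26 weeks from randomization to the first follow-up form and assume that treatment starts at once. With the full 8 weeks of treatment, 26 - 8 = 18 weeks after treatment are covered. With four sessions one week apart, which span 3 weeks, 26 - 3 = 23 weeks are covered. In both cases part of the form covers the treatment period, and a true six months after treatment would run into the 12-month form.

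**The case against.** The strongest reply is that the before-after sentence is permissive and exploratory, and that the same section makes the comparison between randomized arms the main economic analysis. That is right. Nothing in the text feeds the within-arm change into the cost-effectiveness ratio. The trial is also a pilot whose main purpose is acceptability, and the 18 weeks is the extreme case. All of this limits the weight of the point. What it leaves standing is that the article plans a comparison whose expected direction is known in advance and gives it a window that the data do not match.

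Three stronger readings are tempting, and the documents do not support them.

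- *The incremental analysis is biased by the fall.* It is not. The fall is shared by both arms and cancels in expectation, as the table shows.
- *QALYs and costs will go unadjusted for baseline.* The section is silent on covariates and rules nothing out. A journal article may leave this to a fuller plan. A lack of adjustment would not cause the fall and would not bias the randomized contrast. It would cost precision: with an assumed utility SD of 0.30, 49 per arm and baseline to follow-up correlations of 0.3 to 0.7, the SD of the simulated 12-month QALY difference was 0.045 to 0.054 unadjusted and 0.035 to 0.028 adjusted.
- *Six-month costs will be set against 12-month QALYs.* No passage says so. The six-month windows belong only to the exploratory sentence, and service use is collected at the same time points as EQ-5D.

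**Conclusion.** The point holds for the before-after comparison only. A within-arm fall in cost is expected without any treatment effect and cannot be attributed to either intervention. If the index admission is counted, the fall is at least of the order of that admission's cost. Its actual size cannot be taken from the article, which gives no cost data and does not say whether the admission is counted. The part due to regression to the mean rests on the usual assumption that people enrolled at an admission are above their own average use.

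The mismatch of windows follows from the text itself: about 18 to 23 weeks after treatment on the 6-month form, if sessions are weekly at the shortest and treatment starts at randomization. A later start would shorten this.

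This is an improvement to an exploratory analysis. It does not undermine the main economic comparison.

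**What to change.** Replace the before-after comparison with the between-arm difference in costs from randomization to 6 months and from randomization to 12 months, with baseline six-month cost as a covariate. Define all windows from randomization, so that they agree with the questionnaires. If the within-arm change is still reported, label it descriptive, state whether the index admission is counted in the before window, and draw no conclusion about savings from it.

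As advice, the QALY difference could be estimated with baseline EQ-5D as a covariate inside the bootstrap, for precision.

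The cost is a few sentences in the Economic analysis section. Service use and EQ-5D are already collected at baseline, 6 and 12 months, so no new data are needed.
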